#### Sample size

The study is s a superiority trial based on the BREAST-Q domain *Satisfaction with the breast/s*.^25^,^27^ The clinically meaningful difference in BREAST-Q was set to 10 points. There are no anchor-based minimal important differences (MIDs) published for BREAST-Q, but the distribution-based MID is 4 for satisfaction with the breast/s.^28^ The SD was set to 18, as calculated according to US norms.^29^ If power is set to 0.80 and alpha to 0.05, the case-to-control ratio is 1, and a 20% dropout rate is expected, 62 patients are needed in each group (https://riskcalc.org/samplesize/). In the randomised cohort, 124 participants will be randomised 1:1. In the preference cohort, patients will be included until 62 participants have selected the least popular alternative (figure 3). This will result in an overall trial cohort with a minimum of 124 participants in each arm and enough participants in the subgroups *randomised* and *patient preference* to allow for analyses of differences.

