### Study within a trial

The RPPT design will be assessed quantitatively using a SWAT.^22^ This considers the rate of patients fulfilling the criteria and agreeing to participate in the study, the time it takes to recruit the target number in each group, the rate of patients who accept randomisation and differences between the randomisation and preference cohort regarding demographic factors as well as preoperative satisfaction with breasts, expectations, body image, symptoms of depression and anxiety, and generic quality of life. To obtain insights into attitudes towards and experiences of the study process, semistructured interviews will be conducted concerning issues such as how the process can be ameliorated to increase recruitment, retention and follow-up rates of questionnaires, and how the participation information leaflet should be improved to maximise recruitment. Trial participants, participating surgeons and research nurses will be interviewed. Embedded qualitative studies will be used to investigate the participants’ thoughts, attitudes and experiences regarding:

*The choice of breast reconstruction and the choice of reconstructive method*. Participants will be recruited from the preference cohort. Longitudinal—the same participants will be interviewed at allocation and 12 months after the reconstruction.*What makes a participant very satisfied or very dissatisfied*. Participants will be recruited from both cohorts among women who scored high/low, compared with the mean, on BREAST-Q outcome and satisfaction with breast/s.*SWAT*^22^*: How the participant experienced the trial process, how it can be ameliorated to increase recruitment, retention and follow-up rates of questionnaires and how the participation information leaflet should be designed/written to maximise recruitment*. Different participants from both cohorts are interviewed at allocation, 3 and 12 months to explore if there are different themes at different time points.

Qualitative approaches and research paradigms will be chosen based on the type of question studied. Interview guides are given as online supplemental appendix 3. A purposive criterion-sampling technique will be used at the time points described in figure 4. Interviews will follow semistructured interview guides designed for each research question. Participants will be recruited until saturation has been achieved.

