### Statistical methods

A detailed statistical analysis plan will be drafted early in the trial and finalised before primary outcome analysis. All analysis will be performed on an intention-to-treat basis and per-protocol analysis as sensitivity analysis. Descriptive data will be given as appropriate according to type of data and if it is skewed or not. This will also form the basis for statistical tests chosen to compare groups. Sensitivity analysis will be done were missing data in predictors will be handled by multiple imputation methods.^50^ Regression analysis preceded by collinearity check of potential predictors and performed to allow for correction for possible confounders. Residuals for each regression analysis will be checked for the assumptions of normal distribution and constant deviation along the predicted values. Subgroup analyses will be performed for the randomised and the preference cohort and for timing of reconstruction (immediate/delayed reconstruction) and for patients who unexpectedly will require radiotherapy. The statistical analysis will adhere to the Setting Intenartional Standards in Analysing Patient-Reported Outcomes and Quality of Life Endpoints in Cancer Clinical Trials (SISOQOL) framework.^51^ All tests will be two tailed and a p value of ≤0.05 will be considered to indicate a statistical significance.

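### Observed skewness is allowed to choose the between-group test, and the primary comparison is not tied to the preoperative score, although the trial is sized on a 10-point mean difference

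*Protocol article*

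**What the plan says.** The Sample size section describes a "superiority trial based on the BREAST-Q domain" Satisfaction with the breast/s. It fixes the target: "The clinically meaningful difference in BREAST-Q was set to 10 points". It also fixes the spread: "The SD was set to 18, as calculated according to US norms". Both are inputs to a comparison of two means.

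The Statistical methods section first says that descriptive summaries depend on the type of data and on skewness. It then says of that same criterion: "This will also form the basis for statistical tests chosen to compare groups". It names no tests and no threshold for skewness. Regression appears as a way to correct for possible confounders after a collinearity check, and no covariate is listed. Timing of reconstruction appears there only as a subgroup factor. The SAP is to be drafted early and "finalised before primary outcome analysis".

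The preoperative score is available. The Study within a trial section compares the randomised and preference cohorts on demographic factors "as well as preoperative satisfaction with breasts, expectations, body image" and other measures, and the Adherence section has questionnaires handed out at allocation. That cohort comparison is the only use the article names for the preoperative score.

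The same Study within a trial section plans interviews with selected women: "Participants will be recruited from both cohorts among women who scored high/low, compared with the mean, on BREAST-Q outcome" and satisfaction with breast/s. The section on randomisation says that blinding is not possible and that randomisation is simple, so it is not stratified by timing.

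**The concern.** This is a stated rule and not merely a detail left for later. An SAP that follows the sentence inherits a test that depends on the data. An SAP that fixes a model departs from the published protocol. Either way the sentence needs changing for the primary outcome.

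Three things are at stake.

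- **The quantity estimated.** A rank test does not estimate a difference in mean points, which is what the 10-point target refers to. The effect measure reported for the primary outcome would depend on the shape of the collected data.
- **Precision.** In the randomised cohort the reason to adjust is to remove outcome variance that the preoperative score predicts. Framing regression as confounder correction, with covariates still to be chosen, does not secure this.
- **Freedom of choice.** In an unblinded trial, a choice of test and covariates that stays open until the primary analysis is open to question. The interview sampling needs BREAST-Q scores to be compared with a mean, including on the domain used for sizing, and the article does not say that the SAP is final before then.

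**Working it through.** **Inputs from the protocol.** Difference 10, SD 18, two-sided alpha 0.05, power 0.80, ratio 1:1, drop-out 20% (Sample size; two-sided testing from Statistical methods). Stated size: 62 per group.

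**Assumed input.** The correlation r between preoperative and follow-up score is not given. The range shown is 0.2 to 0.5.

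**1. The plan's own figure.** Normal approximation: n = 2 × 18² × (1.960 + 0.842)² / 10² = 50.9, so 51 evaluable per group (the t-test version gives 51.8, so 52). Then 51 × 1.2 = 61.2, so 62, which matches the stated size. Dividing instead, 51 / 0.8 = 63.75, so 64. The stated figure is therefore that of an unadjusted comparison of two means.

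**2. Evaluable patients.** 62 × 0.8 = 49.6 per arm.

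**3. Power with and without the preoperative score.** Residual SD = 18 × √(1 − r²). Standardised difference d = 10 / residual SD. Two-sample t-test power at 49.6 per arm:

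| r | Residual SD | d | Power |
|---|---|---|---|
| 0 (unadjusted) | 18.00 | 0.556 | 0.782 |
| 0.2 | 17.64 | 0.567 | 0.798 |
| 0.3 | 17.17 | 0.582 | 0.819 |
| 0.4 | 16.50 | 0.606 | 0.848 |
| 0.5 | 15.59 | 0.642 | 0.886 |

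A normal approximation at 50 per arm gives slightly higher values: 0.793 unadjusted, then 0.809, 0.829, 0.858 and 0.894.

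**4. Timing alone.** Suppose timing shifts the score by g points and a share p is in one timing group. The variance explained is p(1 − p)g² / 18². For g = 5 and p = 0.5 this is 0.25 × 25 / 324 = 0.019. For g = 10 and p = 0.5 it is 0.25 × 100 / 324 = 0.077. On the normal approximation at 50 per arm, power goes from 0.793 to 0.80 (g = 5) or about 0.82 (g = 10). Both shifts are assumed.

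**5. Does a skewness rule damage type I error?** Simulation with 10,000 runs and 50 per group. The rule was a Shapiro-Wilk check, then a t-test or Mann-Whitney test. The Monte Carlo standard error near 0.05 is √(0.05 × 0.95 / 10,000) = 0.002.

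| Null case | t-test | Mann-Whitney | Fixed rule | Smaller p-value taken |
|---|---|---|---|---|
| Normal scores | 0.048 | 0.044 | 0.048 | 0.055 |
| Skewed scores | 0.052 | 0.048 | 0.049 | 0.066 |

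A fixed rule stays near 0.05. Only taking the smaller p-value raises the error rate, and the protocol does not propose that.

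**The case against.** The strongest reply is that a journal article may leave the primary model, covariates and test to the SAP, and that the SAP promised here may already name them. This stands for anything merely absent. It does not cover the sentence on choosing tests, which is a positive statement. The reply that this sentence is generic also has force. It covers complication grades, HADS, EQ-5D and other outcomes for which a choice by data type is ordinary, and it does not mention a rank test. But it makes no exception for the primary outcome, and a rank test is the usual consequence of skewness.

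A reader might infer four stronger things that the documents do not support.

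- **That the primary comparison will be unadjusted.** Regression with correction for possible confounders is planned, and the preoperative score could be among the covariates. The supportable statement is that no named adjusted model is tied to the primary comparison.
- **That the team will read postoperative scores before the SAP closes.** The text gives no time point for the interviews with high and low scorers, and the figure with the timeline is not shown. The SAP is drafted early and could be final by then. What is missing is a statement that it will be.
- **That the skewness rule inflates type I error.** Step 5 shows that a fixed rule does not. Nor does a rank test always lose power: with a 10-point shift it had 0.77 against 0.79 for the t-test in normal data, but 0.88 against 0.79 in the skewed case simulated. The case against it as primary test is that it answers a different question from the one the trial is sized on.
- **That adjustment is certain to bring power to 0.80.** At r = 0.2 the figure is 0.798.

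Two further limits stand. The pooled correlation is a simplification, because the preoperative score may be taken with a native breast in immediate cases and after mastectomy in delayed ones. And the base of 49.6 per arm applies to the randomised cohort. The article also describes an overall cohort of at least 124 per arm, in which confounder adjustment would be needed for other reasons.

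**Conclusion.** The point holds as a recommended improvement and does not show that the trial is invalid. An unadjusted randomised comparison of means would be valid and would match the sizing. The defect is that the protocol lets data type and skewness choose the test while the trial is sized on a mean difference, and does not tie a preoperative score it already collects to the primary comparison.

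The size is moderate and conditional. In the randomised cohort, with 20% drop-out and SD 18, power goes from about 0.78 to about 0.80, 0.82 or 0.89 at assumed correlations of 0.2, 0.3 and 0.5. That is a gain of roughly 2 to 10 percentage points, mostly from the preoperative score and little from timing alone. The direction is secure for any correlation that is not negligible. The amount is not known from the documents.

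**What to change.** 1. For the primary comparison in the randomised cohort, replace the skewness rule with one prespecified linear model of Satisfaction with breasts. Its terms are allocated method, preoperative score, timing (immediate or delayed) and preoperative score by timing, with robust standard errors. Report the adjusted mean difference in points with its 95% CI. The score-by-timing term lets the preoperative score carry a different weight in immediate and delayed patients.
2. Keep a rank test as a named sensitivity analysis. Limit the sentence on choosing tests by data type and skewness to outcomes other than the primary one.
3. State that the SAP is final, signed and dated before any postoperative BREAST-Q scores are summarised, including for selecting interview participants.

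The cost is protocol and SAP wording and possibly an earlier SAP signature. No new data, visits or patients are needed.

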### Trial design

GoBreast II is a partially RPPT with a superiority framework. Participants who accept randomisation will be allocated to one of the two methods. Participants who do not accept randomisation will be operated with their preferred method. Thus, the study has two cohorts: one randomised and one patient preference (figure 1). The trial is a single-centre study conducted at a university hospital in Sweden. It has embedded qualitative and health economic research questions.

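### The randomised cohort is labelled a subgroup of a pooled cohort and never named as the primary analysis, so the main superiority comparison is open to confounding by preference

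*Protocol article*

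**What the plan says.** Trial design sets the framework: "GoBreast II is a partially RPPT with a superiority framework". Of the women who decline randomisation it says: "Participants who do not accept randomisation will be operated with their preferred method".

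Sample size derives 62 per group for a 10-point difference in satisfaction with the breast/s and applies it first to the randomised women: "In the randomised cohort, 124 participants will be randomised 1:1". Recruitment to the preference cohort runs until 62 women have chosen the less popular method, with no stated ceiling on the other. The section then combines the two: "This will result in an overall trial cohort with a minimum of 124 participants in each arm". In the same sentence it calls the randomised and preference cohorts subgroups and says they are large enough for analyses of differences.

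Statistical methods keeps that hierarchy: "Subgroup analyses will be performed for the randomised and the preference cohort". The cohorts stand there beside timing of reconstruction and unexpected radiotherapy. The section also says that all analyses follow intention-to-treat, and that regression will correct for possible confounders, none of which it names.

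The section on discontinuing or modifying allocated interventions lets a woman move from the randomised to the preference cohort before reconstruction, and analyses her data according to that move.

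**The concern.** An analysis of the overall cohort, with the randomised women as one of its subgroups, is not a randomised comparison. In the preference half, preference determines the method. The Background itself says that receiving the preferred or non-preferred method could affect outcome. Preference may also be related to expectations, body image and preoperative satisfaction, on which the study-within-a-trial section plans to compare the cohorts. Intention-to-treat protects a comparison only where assignment was random, so it gives no protection in that half.

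At stake is which result carries the superiority claim. With no primary cohort named, the pooled result could be taken as the headline, with narrower limits but exposed to selection bias, and the randomised result read as secondary. The choice could even be made after both are known. The switching rule adds to this: if women leave the randomised cohort because of the method they drew, those who remain are no longer the groups that randomisation formed.

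**Working it through.** **Inputs from Sample size and Statistical methods.** Difference 10 points ("The clinically meaningful difference in BREAST-Q was set to 10 points"); SD 18 ("The SD was set to 18, as calculated according to US norms"); two-sided alpha 0.05; power 0.80; ratio 1:1; dropout 20%.

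**1. The plan's own figure.** n per group = 2 × [18 × (1.960 + 0.842) / 10]² = 50.9, so 51. Inflating by 1.2 gives 61.2, rounded up to 62, which matches the plan. Dividing by 0.8 gives 64, two more per group, which does not matter here. The 80% power calculation therefore fits the randomised cohort alone.

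**2. Power after 20% loss.** 62 × 0.8 = 49.6 per randomised arm.
- Randomised cohort, 49 to 50 per arm: 78.5% to 79.3% power for 10 points.
- Pooled cohort at its minimum, 124 × 0.8 = 99.2 per arm: about 97%, but for an estimate that contains any selection bias.

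**3. Interval width.**
- Randomised: SE = 18 × √(2/49.6) = 3.61; 95% half-width 1.96 × 3.61 = 7.1 points.
- Pooled: SE = 18 × √(2/99.2) = 2.56; half-width 5.0 points.

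**4. Effect of residual bias on the pooled result.** With equal cohorts the preference women supply half the information, so a bias b in their contrast moves the pooled estimate by b/2. With a true difference of zero, type I error = 1 − Φ(1.96 − (b/2)/2.56) + Φ(−1.96 − (b/2)/2.56). The documents give no value for b, so all three are assumptions. Four points is the size of the distribution-based minimal important difference that the protocol cites ("the distribution-based MID is 4 for satisfaction with the breast/s"), and 10 points is the design difference.

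| Assumed b | Shift in pooled estimate | Type I error |
|---|---|---|
| 4 | 2.0 | about 12% |
| 5 | 2.5 | about 16% |
| 10 | 5.0 | about 50% |

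The popular preference arm has no ceiling. If choices split 2:1 or 3:1 (assumed), the preference cohort's weight in a cohort-stratified estimate rises to 57% or 60%. A 5-point bias then gives a type I error of about 23% or 26%.

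**5. Comparing effects between cohorts.** Interaction SE = 18 × √(4/49.6) = 5.11. Power is about 50% for a 10-point difference in effect and about 16% for 5 points. Within each cohort, power for a 10-point difference between methods is the 79% of step 2.

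**6. Possible size of switching.** The Background reports preintervention dropout after randomisation of 12.5% to 23% across groups in the department's earlier trial, because of patient or surgeon preference. If similar shares switched cohort here (assumed), that is 62 × 0.125 = 7.75 to 62 × 0.23 = 14.3, or about 8 to 14 women per group.

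**The case against.** A reader might infer that the protocol commits to a pooled primary test and that its main answer is therefore confounded. The documents do not support that. No sentence says that the primary test uses the overall cohort. The Abstract ties the superiority design to the 124 randomised women, Trial design speaks of two cohorts, and an 80% power calculation fits the randomised cohort, not a pooled one with about 97%. A detailed statistical analysis plan is promised before the primary outcome analysis and may name the analysis set. Regression correction is planned, and expectations and body image, two likely confounders, are measured. The bias sizes above are assumptions, and 10 points left after adjustment would equal the whole design difference.

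Most of this stands, and it limits the wording to open to confounding. It does not remove the point. Two sections give the randomised cohort subgroup status and none gives it primary status. An analysis plan that follows those labels inherits the problem, and one that departs from them contradicts the protocol. Adjustment with no named covariates cannot be counted on where preference itself determines treatment.

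Two further inferences go too far. The statement that the subgroups are large enough for analyses of differences is not wrong if it means differences between methods within each cohort. It is weak only if it means differing effects between cohorts, and the sentence does not say which. Nor can one conclude that the economic evaluation rests on pooled data, since that section names no cohort.

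**Conclusion.** The point holds as a defect in how the protocol ranks its analyses. It is not a sample size error, and it does not show that the trial's result will be biased. The randomised comparison was sized as the main test, is labelled a subgroup in two sections, and is named primary nowhere. Following the text leads to a main comparison open to confounding by preference, and the switching rule would weaken even the randomised comparison.

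Type I errors of about 12%, 16% and 50% show the exposure for assumed residual biases of 4, 5 and 10 points, with equal cohorts, SD 18 and 20% loss. They are not forecasts. The matter should be settled before outcome data are seen, because it decides whether the headline result is a randomised one.

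**What to change.** - **Sample size and Statistical methods:** state that the confirmatory analysis is the intention-to-treat comparison of all 124 women as randomised, including those who later switch cohort. Remove the subgroup label from the randomised cohort.
- **Discontinuing or modifying allocated interventions:** reconcile the switching rule with that statement. Women who switch stay in their randomised group for the confirmatory analysis; an analysis that follows the switch can be a sensitivity analysis.
- **Preference cohort:** analyse it separately, with adjustment covariates named in advance.
- **Pooled estimate:** if reported, stratify it by cohort, include a cohort-by-method term, and call it supportive only.
- **Analyses of differences:** say that this means differences between methods within each cohort, and call any comparison of effects between cohorts exploratory (about 50% power for a 10-point interaction).

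The cost is wording in the protocol and agreement with the statistical analysis plan, with no extra patients. The confirmatory interval is wider than the pooled one (half-width about 7.1 against 5.0 points), and power after 20% loss is about 79%.

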### Adherence

Trial participants will be given their scheduled follow-up appointment at hospital discharge, with the following scheduled by post. A reminder text message will be sent prior to the appointments to improve adherence. Patient-reported outcome measure instruments will be given to the patient when they are allocated to treatment and then sent by mail at the subsequent timepoints. Two reminders will be sent to the patients if a questionnaire reply is not received by the hospital. Questionnaires will be given to the participants at allocation and then sent by mail, with up to two reminders, at the remaining timepoints, with reminders to ensure continued participation.

